### Creating comparative cohorts

This study will take an inclusive approach to defining the cohorts for inclusion in the individual-level analysis, identifying deceased patients who had mention of one of the four main disease-related causes of death in their clinical records within the last year of life (cancer, dementia, heart or lung disease). Based on previous analyses^52^ and publicly available national data,^53^ we hypothesise that 22–30% of the EPaCCS cohort will die in the hospital compared with 45–50% in the non-EPaCCS group. The inverse probability of treatment weighting will be used to account for the confounding resulting from the non-random allocation of EPaCCS to the groups and balance characteristics between cohorts.^54^ First, a multivariable logistic regression will be used to determine the propensity score weights. Factors included in the model to estimate propensity scores will include the confounders selected to be included in the main outcome analysis (such as age, sex, ethnicity, deprivation and primary diagnosis). These confounders will be cautiously selected based on thorough discussions with our team, which includes experts in palliative care, input from the patient and public involvement group with lived experience in end-of-life care, and a comprehensive literature search. Then, for each patient inpatient encounter, a weight defined as the inverse of the probability of the treatment they had received will be calculated. The balance of patients’ characteristics will be assessed visually and by examining the standardised mean differences.^55^

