### Data sources

The study will use non-identifiable data from three EPaCCS across three distinct geographical locations in the UK, namely London, Leeds and Bradford, which combined have a population of 10.4 million people. These EPaCCS were introduced at different times within the same city and across different cities. This has led to natural variation in exposure, resulting in datasets that cover varying time periods: 2010–2022 in London, and 2015–2023 in Leeds and Bradford. Nonetheless, these EPaCCS are well established and contain a sufficient number of records, as illustrated in table 1, to enable meaningful individual site analyses and answer our research questions. Additional anonymised EPaCCS data from different regions will be considered if made available during the study. The sample size will be determined by the data available in the three datasets and will vary depending on the analysis.

**Table 1 T1:** EPaCCS and data availability

EPaCCS location	EPaCCS specific data
London EPaCCS	Coordinate My Care (CMC) served as the commissioned EPaCCS in London from 2010 to 2022, during which time it was also the largest UK EPaCCS. Covering 32 CCGs serving a population of 8.9 million, this EPaCCS dataset reflects a diverse urban patient population in terms of diagnosis, ethnicity and socioeconomic background. CMC records comprise data from various healthcare settings, including primary and secondary care, hospices and nursing homes. The dataset encompasses demographics, diagnoses, care preferences, the ceiling of treatment, resuscitation status, living circumstances, prognosis, performance status, date and place of death. Additionally, data is available regarding how often the record was accessed by urgent and non-urgent healthcare workers. In later years, patients had the option of starting a ‘MyCMC’ plan, whereby they use a patient portal to input some data themselves. The anticipated numbers for inclusion in the dataset are 140 000 records, of which 100 000 are for deceased patients.

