Using the CMC-WSIC linked dataset and the Leeds dataset, the study will use a natural experiment approach^33^ and establish cohorts of patients who have died having EPaCCS (case) or not having an EPaCCS (control) in each dataset separately. Place of death will be coded as a binary variable for individual-level analysis, indicating whether death occurred in a hospital or elsewhere. For ecological analysis, rates of hospital deaths per year will be calculated for each one of the eight health boroughs (previously called CCGs) in North West London. Time spent in hospital will be derived as a continuous variable measuring the number of days between admission and discharge within the last 90 days of life, or between admission and death for patients who died in hospitals. Rates of time spent in hospital within the last 90 days of life per year will also be calculated. The cost analysis will use the patient-level cost data available in WSIC. Formal costs will be estimated by combining utilisation frequencies in the data with unit costs for different services.^49^ Informal care hours will be estimated from the literature on end-of-life care populations and associated costs using the substitution method (primary analysis) and opportunity cost method (sensitivity analysis). Intervention costs will be estimated using NHS data.^50^ We will model costs after diagnostic testing of different modelling approaches in the context of distributional characteristics.^51^

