### Sensitivity analysis

We will consider a number of approaches in terms of sensitivity analyses, which will be informed by the availability and completeness of the data.^57^ Sensitivity analyses will be conducted on the cohort identification strategy and our choice of covariates used for estimating the propensity scores.^58^ We will also consider several approaches and sensitivity analysis techniques to deal with unobserved confounding, the implementation of new policies and the effect of the COVID-19 pandemic on both the intervention and the outcomes of interest.^33 59^ In terms of the COVID-19 pandemic, we will build on our previous evaluation,^47^ identify the records created during the pandemic and, if appropriate, perform a sensitivity analysis by potentially excluding these records to assess the impact of this period on our findings.

### Outputs from work package 2

The second work package will provide novel insight into the effect and value of EPaCCS and ACP on end-of-life care quality outcome measures. We will derive high-quality evidence on how the intervention affects costs in a context where a trial is unfeasible. Secondary analysis will provide insights into how end-of-life care interventions may address or exacerbate inequities in the context of systematic gaps.

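### The disease-mention rule for the work package 2 cohorts has no cut-off before death and no common-source requirement, so entry may depend on late hospital contact, and differently by EPaCCS status

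*Protocol article*

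**What the plan says.** All references are to the protocol article.

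- **Entry rule** (Creating comparative cohorts). The individual-level cohorts consist of decedents "who had mention of one of the four main disease-related causes of death in their clinical records within the last year of life"; the conditions are cancer, dementia, heart disease and lung disease. The stated intent is breadth: "This study will take an inclusive approach to defining the cohorts for inclusion in the individual-level analysis".
- **Exposure** (Work package 2). The plan is to "establish cohorts of patients who have died having EPaCCS (case) or not having an EPaCCS (control) in each dataset separately".
- **Outcomes** (same section). The primary outcome is binary, "indicating whether death occurred in a hospital or elsewhere". For the secondary outcome: "Time spent in hospital will be derived as a continuous variable measuring the number of days between admission and discharge within the last 90 days". Where a person dies in hospital, the final stay is counted up to the death.
- **Sources** (Data sources, Table 1). For the London EPaCCS register: "The dataset encompasses demographics, diagnoses, care preferences" and other fields. That register is linked to WSIC, which holds coded primary, secondary, acute, community, mental health and social care data. The Leeds data include linked primary and secondary care records.
- **Planned check** (Sensitivity analysis). "Sensitivity analyses will be conducted on the cohort identification strategy"; which ones is not stated.

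**The concern.** Cohort entry should be settled by facts that precede the outcome and are recorded in the same way in both groups. The rule as written secures neither.

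First, a person can qualify through the admission in which they die. Someone without EPaCCS and without recent coding who is admitted with a cardiac event and dies in hospital acquires a heart-disease mention from that stay. The same person dying at home may acquire none.

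Second, for someone with EPaCCS, a diagnosis field in that record could supply the mention. A control has no such field.

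If both mechanisms operate, controls are selected towards hospital deaths and record-holders are not. EPaCCS would then look protective with no true effect, which is the direction of the study's hypothesis. The same mechanism would act on hospital days and on costs in the last 90 days. Inverse probability weighting reweights only people who have entered, so it cannot restore controls who were never selected.

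**Working it through.** **Timing.** The entry window is the last 365 days of life. The secondary outcome covers the last 90 days and the primary outcome falls on the last day. Both lie wholly inside the entry window, and no earlier cut-off is given.

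**Figures in the plan.** The article gives no power calculation and no capture rates for this rule. It does hypothesise hospital death in 22–30% of the EPaCCS cohort and 45–50% of the non-EPaCCS group. These imply:

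- smallest contrast: (0.30/0.70)/(0.45/0.55) = 0.52, difference −15 points;
- largest contrast: (0.22/0.78)/(0.50/0.50) = 0.28, difference −28 points.

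**Bias formula.** Let e_h and e_n be the probabilities that a record-holder who dies in hospital, or elsewhere, satisfies the rule. Let c_h and c_n be the same for controls. The observed odds ratio equals the true one multiplied by

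F = (e_h × c_n) / (e_n × c_h).

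The observed hospital-death share in controls with true share p is p·c_h / [p·c_h + (1 − p)·c_n], and likewise for record-holders with e_h and e_n.

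**Results with no true effect.** Here p = 45% in both groups, the lower end of the article's range for people without EPaCCS. All capture probabilities are assumptions.

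| e_h, e_n | c_h, c_n | F | EPaCCS share | Control share | Spurious difference (points) |
|---|---|---|---|---|---|
| 1, 1 | 0.98, 0.95 | 0.97 | 45.0% | 45.8% | −0.8 |
| 1, 1 | 0.98, 0.90 | 0.92 | 45.0% | 47.1% | −2.1 |
| 1, 1 | 0.98, 0.85 | 0.87 | 45.0% | 48.5% | −3.5 |
| 1, 1 | 0.98, 0.80 | 0.82 | 45.0% | 50.1% | −5.1 |
| 1, 1 | 0.95, 0.70 | 0.74 | 45.0% | 52.6% | −7.6 |
| 0.99, 0.97 | 0.98, 0.90 | 0.94 | 45.5% | 47.1% | −1.6 |
| 0.98, 0.90 | 0.98, 0.90 | 1.00 | 47.1% | 47.1% | 0.0 |
| 0.98, 0.88 | 0.882, 0.792 | 1.00 | 47.7% | 47.7% | 0.0 |

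For example, in the second row F = 0.90/0.98 = 0.92, and the control share is 0.45 × 0.98 / (0.45 × 0.98 + 0.55 × 0.90) = 0.441/0.936 = 47.1%. With p = 50% the differences change by no more than about 0.1 point.

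The last two rows matter. In the seventh, capture depends on outcome equally in both groups. In the eighth, capture in controls is 0.9 times that in record-holders for both outcomes. In neither is the odds ratio biased, although the hospital-death proportions rise by about 2 to 3 points. Bias in the odds ratio needs the outcome gradient in capture to differ between the groups.

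**The case against.** The strongest reply has four parts.

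1. **The EPaCCS record is not named as a source.** A reader might infer that the rule accepts it, that entry is near-automatic for record-holders, and that controls enter only through late hospital contact. The documents do not support that. The rule speaks only of clinical records. Table 1 lists diagnoses as content of the London register and says nothing about their use for cohort entry; for Leeds it describes no EPaCCS diagnosis field. Both comparison datasets hold primary care data, which should capture many people with these conditions who die outside hospital. This part stands: dependence on exposure is a possibility left open by the wording.

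2. **A window reaching death does not by itself bias the odds ratio.** Correct, as the last two table rows show. But a record created in the last year is itself a clinical contact about serious illness, so fuller capture of those record-holders is plausible, and nothing in the rule prevents it.

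3. **Sources and code lists belong in the analysis plan**, which the article says will be developed. This holds for code lists and the exact source tables. It does not hold for the window, which the article fixes and which overlaps both outcomes.

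4. **Safeguards exist.** The article commits to sensitivity analyses on cohort identification, and the North West London ecological analysis uses total deaths as its denominator, with no mention rule stated. These help, but the sensitivity analyses are unspecified and leave the primary cohort unchanged, and the ecological analysis has no Leeds counterpart.

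**Conclusion.** The point holds in a limited form. The stated entry window overlaps both outcomes, and the rule neither confines the mention to sources common to both groups nor excludes diagnoses found only in the EPaCCS record. Entry may therefore depend on hospital contact in a way that differs by EPaCCS status, and where that happens through fuller capture of record-holders the error favours EPaCCS.

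The size cannot be determined from the documents. Under the assumed capture rates with complete capture of record-holders, the factor on the odds ratio runs from 0.97 to 0.82, with 0.74 as an extreme case; it is 1.00 if the capture pattern is the same in both groups. The spurious differences of about 1 to 8 points are smaller than the hypothesised 15 to 28, so this mechanism would not on its own produce the expected contrast. It could imitate a modest effect where there is none, which matters in a study that aims at credible causal estimates. No calculation was made for hospital days or costs; for those only the direction is argued.

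This should be fixed before the cohorts are extracted. It does not show that the primary result will be biased.

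**What to change.** For the primary individual-level cohort, in both groups:

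- require a coded diagnosis of one of the four conditions dated before the last 90 days of life;
- take it only from primary and secondary care sources available for people with and without EPaCCS, and not from CMC or other EPaCCS fields;
- choose a look-back length before that cut-off and apply it equally to both groups. The length is for the team to decide, because a longer look-back admits long-past diagnoses and changes the target population;
- keep the present rule as one of the named sensitivity analyses on cohort identification.

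If capture is then equal across the groups, F = 1.00. The cost is a change of wording and a different query on data already planned. The downside is that people first diagnosed in the last 90 days leave the primary cohort; the sensitivity analysis under the present rule shows what difference that makes.

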### Work package 2: evaluation of the effect of EPaCCS on place of death and secondary healthcare use at end of life and cost minimisation analysis of EPaCCS (objectives 2A and 2B)

The second work package will adopt a retrospective cohort design under a natural experiment framework to evaluate the effects of EPaCCS on quality indicators of end-of-life care. The quality indicators used in this work package include the place of death (primary outcome) and time spent in hospital in the last 90 days of life (secondary outcome).^48^ The hypothesis for work package 2 is that people with EPaCCS records are less likely to die in hospital and more likely to spend less time in hospital in the last 90 days of life compared with people without EPaCCS records. An EPaCCS record may address one or both sides of the cost-effectiveness ratio; reducing futile or unwanted treatments will save hospital resources while improving goal-concordant care realises more utility. However, there is also the potential for increased costs, notably through substitution effects, for example, if people die in a hospice instead of in a hospital. We therefore hypothesise that EPaCCS improve the cost-effectiveness of care near the end of life.

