### Individual patient-level analyses

Mixed effects logistic regression will be used to assess the effect of EPaCCS on the primary and secondary outcome measures adjusting for covariates associated with these outcomes such as the availability of carers, social determinants of health (age, gender, ethnicity, social deprivation), marital status, living circumstances, place of care and comorbidity. To account for the time-varying nature of implementation, the season/financial quarter will also be included in the model. Marginal ORs for each of the outcomes based on weighted logistic regression will be reported.

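### The inverse-probability weight is defined per inpatient encounter, although the cohort, the exposure and the primary outcome are defined once per decedent

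*Protocol article*

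**What the plan says.** All references are to the Protocol article, work package 2.

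- **Unit of the weight.** *Creating comparative cohorts*: after a logistic regression for the propensity score, "for each patient inpatient encounter, a weight defined as the inverse of the probability of the treatment they had received will be calculated".
- **Unit of the cohort.** The same section builds the individual-level cohort by "identifying deceased patients who had mention of one of the four main disease-related causes of death in their clinical records" (cancer, dementia, heart or lung disease, within the last year of life). It does not ask for an admission.
- **Unit of the exposure.** The work package 2 section will "establish cohorts of patients who have died having EPaCCS (case) or not having an EPaCCS (control) in each dataset separately".
- **Unit of the primary outcome.** Place of death is a binary variable "indicating whether death occurred in a hospital or elsewhere". It occurs once per person.
- **Use of the weights.** *Individual patient-level analyses*: "Marginal ORs for each of the outcomes based on weighted logistic regression will be reported".
- **Hypothesis.** The work package 2 section expects the following, with hospital time counted over the final 90 days: "people with EPaCCS records are less likely to die in hospital and more likely to spend less time in hospital".
- **Expected rates.** *Creating comparative cohorts*: "22–30% of the EPaCCS cohort will die in the hospital compared with 45–50% in the non-EPaCCS group".

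**The concern.** The sentence that defines the weight names a unit that appears nowhere else in the individual-level analysis. The document describes no encounter-level dataset, and it gives no rule for a decedent with no inpatient encounter or with several.

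Three things follow if the sentence is carried out literally. A decedent who was never admitted has no record to carry a weight and cannot enter a weighted model. A decedent with several encounters carries several weights for a single place of death. The reported marginal odds ratio then describes people with an inpatient encounter, possibly counted by encounter, and not decedents with and without EPaCCS.

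The loss would not be neutral. Decedents with no inpatient encounter will mostly have died outside hospital with no hospital days, which is the result that EPaCCS is expected to bring about. For encounters after the record was created, selecting on them means selecting on a consequence of exposure, and a propensity model for EPaCCS status does not repair that.

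**Working it through.** **Text check.** Cohort, exposure and primary outcome are all per decedent. Balance is to be checked on patients' characteristics, and the outcome models stand under a patient-level heading. Only the weight is per encounter. *Sensitivity analysis* varies cohort identification and the propensity covariates, not the unit of weighting. No other section overrides the sentence.

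**Plan's own figures.** The plan states no odds ratio, power or calculated sample size, so there is nothing to reproduce. Its expected hospital-death rates give crude odds ratios among all decedents, with OR = [p1/(1−p1)] / [p0/(1−p0)]:

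- 22% v 45%: 0.35
- 22% v 50%: 0.28
- 26% v 47.5% (midpoints): (0.26/0.74)/(0.475/0.525) = 0.351/0.905 = 0.39
- 30% v 45%: 0.52
- 30% v 50%: 0.43

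**Step 1: restrict to people with an inpatient encounter.** The document gives no admission proportions, so those below are assumptions. Every hospital death is counted as an admitted patient, so P(hospital death | admitted) = P(hospital death)/P(admitted). The figures are crude and take no account of confounding. At the midpoint rates, where the all-decedent OR is 0.39:

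| Assumed admitted, EPaCCS / none | Hospital death among admitted | OR among admitted |
|---|---|---|
| 60% / 60% | 43.3% v 79.2% | 0.20 |
| 70% / 70% | 37.1% v 67.9% | 0.28 |
| 80% / 80% | 32.5% v 59.4% | 0.33 |
| 70% / 80% | 37.1% v 59.4% | 0.40 |
| 60% / 75% | 43.3% v 63.3% | 0.44 |
| 50% / 70% | 52.0% v 67.9% | 0.51 |
| 60% / 80% | 43.3% v 59.4% | 0.52 |

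Worked line (60% / 80%): 0.26/0.60 = 0.433 and 0.475/0.80 = 0.594; odds 0.765 and 1.462; OR = 0.52.

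At 30% v 45% (all-decedent OR 0.52), admission of 50% / 70% gives 60.0% v 64.3% and an OR of 0.83.

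**Step 2: let encounters be the rows.** Assume 60% / 75% admitted, and count each hospital death in one row only. The share of rows ending in hospital death is P(hospital death)/[P(admitted) × mean encounters per admitted patient].

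- 1.3 v 1.3 encounters: 0.26/0.78 = 0.333 and 0.475/0.975 = 0.487; OR 0.53.
- 1.5 v 2.0 encounters: 0.26/0.90 = 0.289 and 0.475/1.50 = 0.317; OR 0.88.
- 1.3 v 1.8 encounters: 0.26/0.78 = 0.333 and 0.475/1.35 = 0.352; OR 0.92.

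The encounter counts are assumptions too. If place of death were instead copied to every row, and within each group people who did and did not die in hospital had the same mean number of encounters, the OR would stay at the step 1 value of 0.44.

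**The case against.** The best defence is that the phrase is a slip. The surrounding text points to one record per decedent: an inclusive cohort of deceased patients, expected rates stated for the whole EPaCCS and non-EPaCCS groups, balance judged on patient characteristics, and a patient-level heading over the models. On that reading the intended analysis is sound and nothing is biased. This stands as a plausible account of intent. It does not remove the point, because the sentence states a rule for the analysis of the primary outcome and the document nowhere corrects it.

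A reader might infer more than the text supports, in five ways:

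- **That the plan excludes never-admitted decedents.** No section says so. Exclusion is only what follows if the sentence is applied literally.
- **That the whole effect would vanish.** An OR of 1.00 appears if one assumes the same share of hospital deaths among the admitted in both groups. With 59% in both and 45% / 80% admitted, 0.45 × 0.59 = 26.6% and 0.80 × 0.59 = 47.2% give 0.40 among all decedents and 1.00 among the admitted. The assumption forces that result. With equal admission the OR moves away from 1.
- **That all admissions are consequences of EPaCCS.** The weighting sentence gives no time window. An admission before the record was created is not a consequence of it.
- **That standard errors would be too small.** The document does not say that repeat encounters are treated as independent. It names mixed effects models, and variance details can properly be left to the analysis plan.
- **That the ecological analysis is affected too.** It uses total deaths as its denominator and does not rest on these weights.

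**Conclusion.** The point holds as an internal contradiction in the rule for the primary individual-level analysis, and it should be corrected before analysis. If the sentence is followed, the weighted marginal OR does not target all decedents. For encounters after record creation, it selects on hospital use, which the plan expects EPaCCS to lower ("more likely to spend less time in hospital in the last 90 days of life"). If it is a drafting slip and one weight per decedent is used in practice, no bias arises.

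The document does not fix the size or the direction. From an all-decedent OR of 0.39 at the plan's midpoint rates, the OR among the admitted runs from about 0.20 to 0.52 over the assumed admission proportions, and is close to unchanged (0.40) at 70% / 80%. It reaches about 0.92 with encounters as rows, under the assumed counts of 1.3 v 1.8 and with each hospital death counted in one row. The expected effect could be exaggerated, hardly altered or nearly lost. These figures show how sensitive the estimate is and do not predict the result.

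**What to change.** In *Creating comparative cohorts*, replace the encounter-based definition with: *for each decedent in the eligible cohort, one weight equal to the inverse of the estimated probability of the EPaCCS status they had.* Add that decedents with no admission are included, with zero hospital days. Carry the same wording into the statistical analysis plan.

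The correction should not be tied to covariates measured before an exposure date. Decedents without EPaCCS have no such date, so that wording could not be applied to them without a separate index-date rule.

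The cost is an edit to one sentence and one added statement. It needs no new data, because the datasets already include all eligible decedents with and without EPaCCS.
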